**4.4.3 Post-treatment follow up period (Day 29 through 64)**

On Day 29, the patient’s treatment arm will be unblinded. Patients who were receiving placebo will end study on Day 29. Patients who were receiving leflunomide will begin the drug elimination procedure: cholestyramine 8 grams orally three times a day for 11 days over the following 14 days. On Day 43, a serum A77 1726 level will be measured to assure elimination of the drug metabolite from the serum. Drug level should be less than 0.02 mg/L (or 0.02 ug/mL). If A77 1726 is less than 0.02 mg/L, the patient will end study on Day 64. If the level is above 0.02 mg/L, the 11 day cholestyramine elimination procedure will be repeated, and the study period will be extended as needed.

During the post-treatment follow up period, patients will come in for study visits on Days 29, 43 and 64. On these days, they will have their histories reviewed, urine will be sent for pregnancy testing when appropriate, and blood will be drawn for safety labs, HIV viral load, CD4+ and CD8+ T cell counts. On Days 29 and 43, blood will also be drawn for research studies of lymphocytes including expression of Ki67, expression of activation markers, memory/naïve phenotyping, expression of coreceptors (CCR5 and CXCR4), ELISA for IL-7, TNF level, lymphoproliferative responses, Annexin V staining and *ex vivo* BrdU as well as for measurement of A77 1726. On Days 29 and 43 they will undergo comprehensive physical exams and on Day 64 a targeted physical exam.

Table 1. Procedures

|  | Scr | H&P | D11 | D15 | D29 | D432 | D642 |
| --- | --- | --- | --- | --- | --- | --- | --- |
| Screening consent | X |  |  |  |  |  |  |
| Standard consent |  | X |  |  |  |  |  |
| History | X | X | X | X | X | X | X |
| Comprehensive physical exam |  | X |  |  | X | X |  |
| Targeted physical exam |  |  | X | X |  |  | X |
| EKG and CXR | X |  |  |  |  |  |  |
| HLA testing | X |  |  |  |  |  |  |
| Safety labs3 | X | X | X | X | X | X | X |
| Urine pregnancy test4 | X | X | X | X | X | X | X |
| HIV ELISA5 | X |  |  |  |  |  |  |
| Hep B, C serology6 | X |  |  |  |  |  |  |
| Lipid panel | X |  |  |  |  |  |  |
| HIV viral load | X | X | X | X | X | X | X |
| Flow cytometry | X7 | X7 | X8 | X8 | X8 | X8 | X7 |
| Additional studies9 |  |  | X | X | X | X |  |
| A77 1726 level |  |  | X | X | X | X |  |

1. On Day 1, blood will be drawn prior to administration of study drug
2. Day 43 and 64 visits will occur only for patients who receive leflunomide
3. CBC with differential, acute care panel, hepatic and mineral panels, amylase, lipase, PT and PTT, urinalysis
4. Serum pregnancy testing can be used if urine is not collected
5. If ELISA positive, proceed with Western blot
6. Hepatitis B surface antigen, hepatitis C antibody, hepatitis C PCR
7. CD4+ and CD8+ T cell counts
8. CD4+ and CD8+ T cell counts, proliferation by intracellular Ki67 expression, expression of activation markers (CD25, CD38, HLA-DR), memory-naïve phenotyping, expression of CCR5 and CXCR4
9. ELISA for IL-7, TNF serum levels, lymphoproliferative responses, Annexin V staining, *ex vivo* BrdU

# 5. 0 Study Population

Eighteen HIV-1 infected patients with CD4+ cell count 350 cells/mm3 and HIV viral load 1,000 copies/mL who are not on any antiretroviral medications will be enrolled on this study.

# 5.1 Inclusion Criteria

1. Age > 18 and ≤ 65 years
2. HIV infected

1. CD4+ cell count 350 cells/mm3 at screening and historical nadir (since diagnosis of HIV) of 200 cells/mm3
2. Plasma HIV viral load 1,000 copies/mL at screening
3. Ability to understand and sign informed consent and willingness to comply with the study requirements and clinic policies
4. Must have a primary care physician who will be taking care of the patients for their HIV infection
5. Female study subjects of reproductive potential (defined as girls who have reached menarche or women who have not been post-menopausal for at least 24 consecutive months, i.e., who have had menses within the preceding 24 months or have not undergone a sterilization procedure (hysterectomy or bilateral oophorectomy), must have a negative serum or urine pregnancy test.
6. Agreement not to participate in a conception process (eg. active attempt to become pregnant or impregnate, sperm donation, or in vitro fertilization) and to follow strict contraceptive measures while on study.
7. If participating in sexual activity that could lead to pregnancy, the study volunteer must agree that two reliable methods of contraception will be used simultaneously during the entire study. Acceptable forms of contraception include:

- Condoms (male or female) with or without a spermicidal agent. Condoms are recommended because their appropriate use is the only contraception method effective for preventing HIV transmission.
- Diaphragm or cervical cap with spermicide
- IUD
- Hormonal-based contraception

Study subjects who are not of reproductive potential (women who have been post-menopausal for at least 24 consecutive months, women who have undergone hysterectomy or bilateral oophorectomy, or prepubescent boys or men who have documented azoospermia) are eligible without requiring the use of contraception. Written or oral documentation communicated by clinician or clinician’s staff of one of the following:

- Physician report/letter.
- Operative report or other source documentation in the patient record (a laboratory report of azoospermia is required to document successful vasectomy).
- Discharge summary.
- Laboratory report of azoospermia.
- FSH measurement elevated into the menopausal range as established by the reporting laboratory.

# 5.2 Exclusion Criteria

1. Current treatment with antiretrovirals or use of antiretrovirals within 12 weeks of screening
2. Intention to start antiretroviral regimen within 64 day study period
3. Previous treatment with leflunomide
4. Previous treatment with IL-2
5. Treatment with immunomodulatory agents (including hydroxyurea, mycophenolate, cyclosporine, rapamycin, anti-HIV vaccines, interleukins other than IL-2, interferons) within 60 days of study
6. Treatment with systemic corticosteroids within 30 days of study
7. Inability or unwillingness to discontinue drugs (except NSAIDs) that are metabolized by P450 2C9 isoenzyme (see Appendix A - Medications Metabolized by CYP 2C9 and Contraindicated During Treatment Period).
8. Inability or unwillingness to discontinue hepatotoxic drugs (eg. isoniazid, rifampin, HMG CoA reductase inhibitors)
9. Inability or unwillingness to discontinue drugs that interact with cholestyramine (eg. have diminished absorption with cholestyramine) (see Appendix B – Medications that Have Interactions with Cholestyramine)
10. Current use of or known intolerance of cholestyramine or bile acid sequestering resins
11. History of familial hyperlipoproteinemia type III, IV or V
12. Active bacterial infection within 4 weeks of screening
13. History of AIDS-defining illness (category C) (see Appendix C - CDC AIDS Classification Criteria)
14. Hepatitis B or C infection
15. Acute or chronic liver disease from any cause (eg. alcoholic hepatitis or alcohol induced cirrhosis, autoimmune hepatitis, primary biliary cirrhosis, sclerosing cholangitis, Wilson’s disease, hemochromatosis) which the investigator feels would compromise the subject’s safety
16. History of biliary obstruction
17. Current alcohol abuse or unwillingness to abstain from alcohol use for study period
18. History of hypertension that is not controlled (<140/80 mm/Hg) on a single antihypertensive agent
19. Abnormal laboratory findings: hemoglobin <10 g/dL; ANC <1000/mm3; platelets <100,000/mm3; creatinine above the upper limit of normal; ALT or alkaline phosphatase >1.25 times the upper limit of normal; AST >1.25 times the upper limit of normal* direct bilirubin >1.5 times the upper limit of normal; total bilirubin >2 times the upper limit of normal lipase > 1.5 times the upper limit of normal; PT >1.1 times the upper limit of normal; PTT>1.5 times the upper limit of normal.
20. History of malignant neoplasm except in situ anogenital carcinoma, adequately treated basal or squamous cell carcinoma of the skin or solid tumors treated with curative therapy and disease free for at least five years
21. Significant medical or psychiatric disorder which the investigator feels would interfere with the subject’s ability to participate or would compromise safety
22. Women who are currently pregnant or breast-feeding
23. History of interstitial lung disease

* Subjects with isolated AST elevation, higher than normal CPK values in the absence of liver disease and compatible history such as intense exercise will be allowed to re-screen if the study investigators suspect that the elevated AST is of muscular origin.

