**6.3 Criteria for stopping study drug and immediate institution of drug elimination procedure**

If a patient meets any of the following criteria for stopping study drug, his dosing assignment will be unblinded and if he was receiving leflunomide, he will be started immediately on the drug elimination procedure:

1. Patient develops malignancy or serious infection
2. Patient becomes pregnant
3. Patient develops elevation of liver enzymes greater than 2X the upper limit of normal (if liver enzymes are 3 X the upper limit of normal the study drug will be stopped immediately; if liver enzymes are >2 but <3 X the upper limit of normal, they will be repeated in 24 to 72 hours and if they remain >2 X the upper limit of normal the study drug will be stopped)
4. Patient develops grade III or IV adverse event or toxicity
5. Patient develops grade II or greater allergic reaction or urticaria
6. Patient develops a drop in CD4+ T cell count of 40% of baseline or a CD4+ T cell count of <200 that is confirmed with a second measurement (after 10-14 days) [Baseline CD4+ T cell count = average of CD4+ T cell count at H&P and Day 1]
7. Patient develops a medical condition that in the opinion of the investigator indicates that discontinuing the study drug is in the subject’s best interest

Additional criteria for stopping study drug:

1. It is felt by the principal investigator to be in the patient’s best interest, even if the patient does not agree
2. The patient begins taking any of the contraindicated medications listed in Appendix A or B or any other medication listed as an exclusion criteria and does not agree to discontinue it
3. The patient begins taking antiretroviral medications
4. Patient desire to leave study
5. Patient noncompliance
6. Termination of study

At the time of withdrawal from study, a member of the study team (the study coordinator, principal investigator, associate investigator or covering physician) will contact the pharmacy for unblinding of treatment arm (PDS during business hours Monday through Friday or inpatient pharmacy after hours and on weekends). If a patient was receiving leflunomide, oral cholestyramine 8 g three times daily will be administered for a total of 11 days. Serum A77 1726 level will be measured upon completion of this procedure. If the A77 1726 level is above 0.02 mg/L, the elimination procedure will be repeated.

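### Section 5.1 accepts hormonal contraception as one of two methods for the whole study, but exclusion 9 with Appendix B requires women to be willing to stop it

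*Protocol*

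**What the plan says.** Protocol 5.1 (contraception item, numbered 7) requires of anyone whose sexual activity could lead to pregnancy that "two reliable methods of contraception will be used simultaneously during the entire study". It names four acceptable options: condoms, diaphragm or cervical cap with spermicide, IUD, and "Hormonal-based contraception". The last carries no limit on route or study period. One list serves both men and women.

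Protocol 5.2, exclusion 9, excludes for "Inability or unwillingness to discontinue drugs that interact with cholestyramine (eg. have diminished absorption with cholestyramine" and points to Appendix B (11.2). That appendix includes estrogens and progestins as bare entries.

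Protocol 6.3 gives, among the additional reasons to stop study drug, "The patient begins taking any of the contraindicated medications listed in Appendix A or B", together with a second condition: that the patient will not agree to stop the medication.

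Protocol 4.4.3 starts elimination in leflunomide patients on Day 29 with "cholestyramine 8 grams orally three times a day for 11 days over the following 14 days". It adds: "If the level is above 0.02 mg/L, the 11 day cholestyramine elimination procedure will be repeated". For the safety stops in 6.3, a patient on leflunomide is unblinded and "he will be started immediately on the drug elimination procedure". Protocol 9.3.1.1 reports the box warning that pregnancy is to be avoided until elimination is complete.

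**The concern.** A woman whose two methods are a condom and a hormonal contraceptive satisfies 5.1 for the whole study. Under exclusion 9 she is eligible only if she is willing to give up the hormonal one. A site that reads 5.1 alone would go on counting that method while she takes a resin that the protocol itself lists as interacting with it. A site that reads exclusion 9 alone would have her stop it, on a date of the site's own choosing.

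The rule at issue is pregnancy prevention for a drug that 9.3.1.1 describes as capable of fetal harm and contraindicated in women who are or may become pregnant. The uncertainty falls in the period when the metabolite is still being cleared.

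**Working it through.** The plan gives no figure on this point. The check is a comparison of provisions, followed by simple arithmetic on the size of the issue.

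**1. The provisions side by side**

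| Place | Rule for a woman on a hormonal method | Limit or exception stated |
|---|---|---|
| 5.1, contraception item | May count it as one of two, whole study | None |
| 5.2, exclusion 9, with Appendix B | Must be willing to discontinue it | None: no route, no stop date |
| 6.3, additional stopping reasons | Study drug stops if she begins it on study and will not give it up | Does not reach a woman already using it at entry |

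The conflict therefore rests on the first two rows. Section 6.3 adds one narrow case.

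**2. Does anything else settle it?**
- Exclusion 7 shows that the protocol writes an exception when it wants one: NSAIDs are exempted from the CYP 2C9 rule, and Appendix A explains why. Exclusion 9 has no counterpart.
- Section 4.4.2 sets a stop date of one week before Day 1 but refers only to Appendix A. Appendix B drugs have no stop date.
- Section 9.3.1.2 advises taking other drugs an hour before, or 4-6 hours after, cholestyramine. This is spacing, not discontinuation, and it does not mention contraception. If the three daily doses are evenly spaced (an assumption), the interval is 24/3 = 8 hours, and the permitted gap is 8 - 6 - 1 = 1 hour to 8 - 4 - 1 = 3 hours. The advice has meaning only for oral products.

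None of these says which rule governs.

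**3. How many patients**
- Leflunomide arm, the only one given cholestyramine (4.3, 4.4.3): 12/18 = 67%.
- The share of these who are women on a hormonal method is not given. Assumed range 5% to 25%: 0.05 × 12 = 0.6 to 0.25 × 12 = 3 patients.

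**4. How long**
- Nominal window, start of elimination to the clearance level: 43 - 29 = 14 days.
- Eleven consecutive dosing days from Day 29 end on Day 39, so the earliest level after a full course is Day 40: 40 - 29 = 11 days.
- The follow-up visit window is plus or minus 7 days (4.4.2), so the latest is Day 43 + 7 = Day 50: 50 - 29 = 21 days.
- A level above 0.02 mg/L adds a further 11 dosing days.

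**5. How fast exposure falls**
- At the one-day half-life on cholestyramine (1.4): 2^-2 = 25% left after 2 days; 2^-11 = 0.05% after 11 days.
- Healthy-volunteer figures (9.3.1.2; 24 hours of dosing, fall of 49-65% in 48 hours): 1 - 0.65 = 35% to 1 - 0.49 = 51% left at 48 hours.

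Most of the remaining exposure lies in the first days of cholestyramine, when the interaction also begins.

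**The case against.** The best defence is that eligibility criteria are cumulative. The list in 5.1 serves men and women alike, and exclusion 9 then narrows it: a woman agrees to stop an interacting hormone and still keeps two methods, choosing from condom, diaphragm or cap, and IUD. On that reading only a cross-reference is missing. The reading is reasonable, but the protocol does not state it. It also does not remove the words in 5.1 that accept the hormonal method for the whole study, and it gives no date for the switch.

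The safeguards are real. A second method is always required, Table 1 schedules a pregnancy test at every visit including Days 29, 43 and 64, and metabolite levels fall quickly. They lower the risk without telling a site which rule to apply. Consent pages are not among the documents at hand, so instructions given there cannot be checked. The disagreement between 5.1 and exclusion 9 does not depend on them.

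Four stronger readings are tempting and are not supported:
- *Contraception fails during elimination.* The protocol gives neither the loss of reliability nor the routes affected. Its example of reduced absorption fits oral products, and nothing shows that implants, injections or patches are affected.
- *Section 6.3 takes every hormonal user off study drug.* It needs both starting the drug on study and not agreeing to stop it.
- *Women learn too late that they need another method, because on Day 29 the "treatment arm will be unblinded".* Exclusion 9 applies before randomization and to both arms, so willingness to discontinue is settled at eligibility. What remains is the missing stop date.
- *The trial's results are affected.* Nothing here touches the sample size or the primary analysis.

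**Conclusion.** The point holds as a conflict between two stated criteria on pregnancy prevention, and it should be fixed. It is more than missing detail, because following one rule as written means disregarding the other.

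Its size is modest: between about 0.6 and 3 patients if the assumed 5% to 25% share is right, for 11 to 21 days if one course of cholestyramine suffices and elimination starts on Day 29. The share is an assumption with no source in the protocol, and the true number could be zero. The conclusion itself depends on none of these figures. It rests only on the wording of 5.1, exclusion 9 and Appendix B.

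**What to change.** State in 5.1 that, for female participants, hormonal methods do not count toward the two required methods from the start of cholestyramine (Day 29 or an early stop) until A77 1726 is confirmed below 0.02 mg/L. Two other listed methods are to be agreed at eligibility and in use throughout that window.

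In the same amendment, change exclusion 9, 6.3 and Appendix B so that contraceptive hormones are exempt from discontinuation on that condition. This part cannot be optional: without it, exclusion 9 still contradicts 5.1 for Days 1 to 28. The simpler alternative is to remove hormonal methods from the counted list for female participants throughout. Under either version the entry stays valid for female partners of male participants. The new text should also say how a hormone-releasing IUD is classed, since 5.1 lists IUDs and hormonal methods separately.

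The cost of the main version is one sentence in 5.1 and matching changes in three places. Some women would add a second non-hormonal method for about 2 to 3 weeks, longer if elimination is repeated. Under the alternative they would need it for the whole study.

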**9.3.1.2 Cholestyramine**

Cholestyramine is a bile acid sequestrant and is used in the leflunomide elimination procedure. When given at a dose of 8 g three times a day for 24 hours to healthy volunteers, cholestyramine decreased the plasma levels of A77 1726 by 40% at 24 hours and by 49-65% in 48 hours.

As indicated in the package insert (submitted separately), use of cholestyramine is contraindicated in patients with complete biliary obstruction, hyperlipoproteinemia types III, IV, or V, or known hypersensitivity to bile acid sequestering resins.

The most common adverse reactions caused by cholestyramine are gastrointestinal including constipation, abdominal discomfort, nausea, flatulence, vomiting, diarrhea, heartburn, anorexia, and indigestion. Mild steatorrhea may also occur. Constipation is the most common complaint of cholestyramine users. Cholestyramine should be used with caution in patients with constipation at baseline, and routine use of a stool softener should be considered with long term use of cholestyramine. Complete intestinal obstruction has been reported in a couple of patients.

Other adverse effects of cholestyramine include rare reports of hematologic effects. Bleeding tendencies due to hypoprothrombinemia have been reported as well as one case of platelet gigantism.

Hyperchloremic acidosis has been reported to occur in small children and older adults receiving concomitant spironolactone therapy.

Elevated thyrotropin levels with a corresponding reduction in serum free thyroxine values occurred in a few hypothyroid patients who were receiving thyroid hormone and cholestyramine concurrently. It is unknown if the alteration in the thyroid function tests were due to a drug interaction or an alteration of thyroid function.

Cholestyramine may interfere with normal fat absorption and thus prevent absorption of fat soluble vitamins A, D, E, and K.

Sipping or holding the resin in the mouth for prolonged periods may lead to changes in the surface of the teeth resulting in discoloration, erosion of enamel or decay.

There is one reported case of urinary tract calculi associated with cholestyramine therapy.

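### Exclusion 11 limits the lipid bar to familial disease, while section 9.3.1.2 states the cholestyramine contraindication without that limit

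*Protocol*

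**What the plan says.** **The exclusion.** Protocol section 5.2, item 11, bars a candidate with "History of familial hyperlipoproteinemia type III, IV or V".

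**The contraindication.** Section 9.3.1.2, summarising the package insert, says that cholestyramine is "contraindicated in patients with complete biliary obstruction, hyperlipoproteinemia types III, IV, or V, or known hypersensitivity to bile acid sequestering resins". It names the lipoprotein types alone.

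**The use of cholestyramine.** Section 4.4.3 puts every patient who was on leflunomide through the elimination procedure from Day 29: three 8 g doses a day for 11 days, repeated if the A77 1726 level is still above 0.02 mg/L. Section 6.3 requires the same course when a leflunomide patient is withdrawn. Neither section makes an exception for a patient in whom the resin is contraindicated.

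**The discretionary exclusion.** Section 5.2, item 21, begins "Significant medical or psychiatric disorder which the investigator feels would interfere with the" and goes on to cover both taking part in the study and safety.

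**The concern.** Items 10, 11 and 16 of section 5.2 appear to be there to keep out people who cannot safely take the elimination drug. Item 11 does this less completely than section 9.3.1.2 calls for. A person known to have type III, IV or V hyperlipoproteinemia that is not familial falls inside the contraindication and outside the exclusion.

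The difficulty would surface late. Such a patient could be randomized and treated for 28 days, and the conflict would appear only when cholestyramine was due. By then the metabolite is in the blood with a half-life of about two weeks (section 1.4), and cholestyramine is the only elimination procedure that the protocol describes. The investigator would have to give a drug that the protocol calls contraindicated, or depart from the protocol.

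**Working it through.** No formula applies and there is no planned figure to reproduce. The check is to compare the texts and then look for another criterion that closes the gap.

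**Step 1. Match each contraindication in section 9.3.1.2 to an exclusion in section 5.2.**

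| Contraindication (9.3.1.2) | Exclusion (5.2) | Comparison |
|---|---|---|
| Complete biliary obstruction | Item 16: "History of biliary obstruction" | Broader: any obstruction, past or present |
| Known hypersensitivity to these resins | Item 10: "Current use of or known intolerance of cholestyramine or bile acid sequestering resins" | At least as broad |
| Hyperlipoproteinemia type III, IV or V | Item 11: familial disease of those types | Narrower by one word |

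Of the three, two are matched or exceeded and one is narrowed.

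**Step 2. Look for another specific criterion that bars the condition.**

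- Item 19 begins "Abnormal laboratory findings: hemoglobin <10 g/dL; ANC <1000/mm3; platelets <100,000/mm3; creatinine above the upper limit of normal". Its full list sets limits on hemoglobin, ANC, platelets, creatinine, ALT, alkaline phosphatase, AST, direct bilirubin, total bilirubin, lipase, PT and PTT. That is 12 tests, of which 0 are lipids.
- Item 8 concerns "Inability or unwillingness to discontinue hepatotoxic drugs (eg. isoniazid, rifampin, HMG CoA reductase inhibitors" and similar agents. A candidate who agrees to stop a statin passes.
- Item 9 concerns "Inability or unwillingness to discontinue drugs that interact with cholestyramine". Appendix B lists fenofibrate, bezafibrate and niacin among these. Again, a candidate who agrees to stop passes, with the lipid disorder still present.
- Item 21 can reach the condition itself, but only through the investigator's judgement.

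The inclusion criteria do not mention lipids. Item 21 is therefore the only remaining route that can bar the disorder as such.

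**Step 3. Ask what screening would show.** Section 4.4.1 includes a lipid panel with triglycerides among the screening tests, and a history is taken before randomization. The investigator therefore sees lipid values in time to act. No exclusion limit is attached to them, so the panel makes an overlooked case less likely but does not close the gap in the text. Table 1 schedules this panel at screening only.

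**Step 4. Count who could be exposed.** Section 4.3 plans 18 patients, 12 on leflunomide and 6 on placebo. Placebo patients leave on Day 29 without cholestyramine (section 4.4.3). The ceiling is thus 12 patients, and a candidate admitted through the gap has a 12/18 = 2/3 chance of assignment to leflunomide. The protocol gives no prevalence of non-familial type III, IV or V disease, so the expected number cannot be computed. The possible range is 0 to 12, and 0 is quite plausible.

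**The case against.** The strongest reply is that *familial* is only part of the disorder's label. Item 11 repeats exactly the three types named in section 9.3.1.2, and items 10 and 16 track the other two contraindications, so item 11 may simply be meant to transcribe the third. Nothing in the protocol separates familial from acquired disease or shows an intention to admit acquired cases. This stands as a fair account of what the authors may have meant. It does not remove the mismatch, because section 9.3.1.2 names the same types without the word and the protocol nowhere says that the two are equivalent. If the reply is right, deleting the word changes nothing in practice.

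A second reply is that harm is unlikely. The case in question is a known diagnosis, the lipids are measured, item 21 is available, and section 9.3.1.2 itself states the contraindication. This also stands and limits the weight of the point. What remains is that one of three stated contraindications to a required drug rests on discretion, while the other two have their own criteria.

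A third reply is that the package insert was submitted separately and is not at hand, so whether it reaches secondary disease cannot be checked. That limits any clinical claim. The inconsistency within the protocol does not depend on it.

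Three stronger readings are tempting and are not supported:

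- A reader might infer that the protocol deliberately admits patients with acquired disease. No text says so.
- A reader might infer that such patients would enter unnoticed. The screening lipid panel and the history argue against that.
- A reader might infer a demonstrated risk of injury. Among the adverse effects of cholestyramine in section 9.3.1.2, none is described as arising in patients with hyperlipoproteinemia.

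**Conclusion.** The point holds as a minor inconsistency of safety and eligibility wording. Item 11 is narrower than the contraindication in section 9.3.1.2, and read literally it leaves known non-familial type III, IV or V disease to the investigator's discretion under item 21. At most 12 planned patients could be exposed; the actual number is unknown and may be zero.

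The conclusion rests on two assumptions: that item 11 is applied as written, and that section 9.3.1.2 states the contraindication as the protocol intends it. Sample size, power and the primary analysis are unaffected.

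**What to change.** Delete *familial* from section 5.2, item 11, so that it reads: *History of hyperlipoproteinemia type III, IV or V*. Nothing else needs to change. There is no need to add an acquired category, which would require a definition that the protocol does not have, or a triglyceride limit.

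The cost is one amended eligibility line, applied to the history already taken at screening, with no extra visit, test or blood draw. The downside is that a few candidates may be excluded. Because the item keeps *History of*, these could include people whose disorder has resolved, which is how item 16 already treats biliary obstruction.
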